#### Summative evaluation: primary data

The primary data for the summative evaluation will be collected by two standardised cross-sectional patient surveys in the intervention group pre and post implementation. Patients who visited the GP practice before implementation of the intervention act as a pre-implementation baseline. After implementation, a second patient survey will be conducted in the same GP practices (post implementation). The summative evaluation using primary data addresses the following research question:

Do patients in GP practices post-implementation report better vaccine literacy than patients pre-implementation?

Vaccine literacy is defined as a secondary outcome, as an association with vaccination uptake is known from the literature [29, 30].

### Formative evaluation

The formative evaluation is conducted using primary data and will examine various elements of the intervention and its implementation [26, 27].

#### Formative evaluation: primary data

The formative evaluation aims to answer the following questions:

How do the GPs and medical assistants rate the feasibility and usefulness of the intervention components? Which components need improvements?Have vaccination procedures improved in GP practices from the perspective of GPs and medical assistants, and which intervention components are assessed as effective?How do patients perceive the information and motivation for vaccination in the GP practices, especially in the GP-patient communication?

The formative evaluation is designed as an accompanying observational study in which the perspectives of the patients, the GPs, and medical assistants on the intervention and its implementation will be explored using qualitative interviews (with patients, GPs, and medical assistants) and quantitative surveys (patients, GPs, and medical assistants).

### Sample

Estimating the effect on vaccination uptake rates to be achieved by the complex intervention is not trivial. From meta-analyses, it is known that effects of around 5% can be achieved by campaigns or interventions that distribute information in a study group, e.g., in the form of brochures, billboard advertisements, flyers, postcards, newsletters, but also by interpersonal communication between GP and patient as well as community education (seminars at schools, workplace) [31]. However, it must be considered that the study results known so far from the literature do not explicitly focus on vaccination. It is not yet known how the COVID-19 pandemic will affect vaccination uptake of established STIKO vaccines in the short and medium term. Due to the above-mentioned, hardly calculable development and the unpredictable development in GP practices, the achievable effect of the project must be estimated conservatively. This is even more important since the data used to estimate the number of cases reflect the situation before the pandemic.

Thus, it is assumed in the following that the influenza vaccination uptake rate as primary outcome increases by 3% as a result of the intervention. This 3%-increase should be seen as an initial change. To detect this effect in the secondary data analysis with a power of 90% at a significance level of alpha = 5% (two-sided), 17,508 patients would be needed without considering the cluster effect. Based on available anonymised data from previous studies [32, 33], the intra-cluster correlation (ICC) is expected to be 0.08. With a mean cluster size of 48 patients per practice vaccinated against influenza on average, this results in a design effect of 4.76 and a corresponding required case number of 83,338 patients. Accordingly, about 1736 GPs would be needed (868 GPs in the intervention and control groups each). Likewise, an increase of 3% is also targeted for increase in vaccination uptake rate of further recommended vaccinations as the secondary outcomes. Since the assumed cluster size is reduced to 28, resulting in a design effect of 3.16 with an ICC of 0.08, a case number of 55,325 patients is required for these analyses. For this, 1976 GPs are needed according to the cluster size – 988 GPs in each of the intervention and control groups. Therefore, due to the smaller cluster size for the secondary outcome, a total of 988 GPs is required for the intervention group for the analysis. To ensure that the required number of cases will be achieved, an additional 7% (69 GPs) was added to the calculated number of cases. This resulted in a required total number of 1057 GPs per group.

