## Background

With older age the prevalence of chronic conditions such as diabetes mellitus or cardiovascular problems is increasing. At the same time, the age-associated weakening of the immune system contributes to an increased incidence and severity of infectious diseases. Therefore, severe courses or life-threatening complications from infections occur more frequently with older age [1–4]. Infections such as seasonal influenza can therefore last longer or run a more severe course, with serious health risks such as pneumonia or myocarditis. In addition, the risk of secondary diseases (e.g., sepsis as a result of influenza or pneumococcal infection) is higher in patients aged 60 and older. There is also a significant increase in mortality as well as hospitalization among elderly people infected with influenza [5]. The COVID-19 pandemic also shows the increased vulnerability of people in older age to new pathogens [6, 7]. For these reasons, the uptake of existing vaccinations for patients aged 60 and older is of major relevance for preventing the aforementioned severe consequences.

In Germany, the current uptake of vaccinations that are recommended for this age group according to the Standing Committee on Vaccination (STIKO; seasonal influenza, pneumococci, herpes zoster and revaccinations against tetanus, diphtheria and pertussis) is unsatisfactory [8]. In particular, the annual influenza vaccination rate is low in the age group 60 and older (influenza season 2020/2021: 47.3%) and far from the rate of 75% recommended by the Council of the European Union [8, 9]. The rates for pneumococcal vaccination in Germany are low and vary widely between 14.8% and 40.4% depending on the region in the age group between 60 and 73 years [8]. The vaccination rate against herpes zoster in the German population over 60 years is generally extremely low, in the single digits [8].

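### The base sample size of 17,508 does not follow from the printed 3% increase, 90% power and two-sided 5% alpha, and every later figure inherits it

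*Protocol article*

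**What the plan says.** All of the calculation is in the section Sample of the protocol article.

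- Effect: "it is assumed in the following that the influenza vaccination uptake rate as primary outcome increases by 3% as a result of the intervention". The section does not say whether this is in percentage points or relative, and it gives no baseline rate.
- Error rates: "with a power of 90% at a significance level of alpha = 5% (two-sided").
- Base number: "17,508 patients would be needed without considering the cluster effect".
- Clustering: "the intra-cluster correlation (ICC) is expected to be 0.08", and "With a mean cluster size of 48 patients per practice vaccinated against influenza on average". This leads to a design effect of 4.76, 83,338 patients and 1736 GPs, 868 in each group.
- Secondary outcomes: a 3% increase is again targeted, with cluster size 28, design effect 3.16, 55,325 patients and 1976 GPs, 988 in each group.
- After a 7% reserve: "This resulted in a required total number of 1057 GPs per group".

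The only influenza rate in the article is in Background: "influenza season 2020/2021: 47.3" per cent, for people aged 60 and older. Sample notes that the data behind the calculation predate the pandemic, so 47.3% is not stated to be the planning rate.

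**The concern.** The article prints a complete calculation, so a reader should be able to recover the base number from its inputs. The steps after it can be recovered; the base number cannot. Because 83,338, 55,325, 1736, 1976, 988 and 1057 are all built on it, the stated 90% power is not shown to be a property of the design.

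The direction of the error depends on what 3% means. If it means percentage points, the trial is larger than its stated target requires. If it is relative and the baseline is near the national rate, the trial is well short of 90% power. A null result would be read quite differently in the two cases, and the Discussion says the results will inform a decision on inclusion in standard care.

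**Working it through.** **1. The plan's own chain.**
- Primary: 1 + 47 × 0.08 = 4.76; 17,508 × 4.76 = 83,338; 83,338 / 48 = 1736; 1736 / 2 = 868.
- Secondary: 1 + 27 × 0.08 = 3.16; 17,508 × 3.16 = 55,325; 55,325 / 28 = 1976; 1976 / 2 = 988; 988 × 1.07 = 1057.

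Every step reproduces. The halving at the end shows that 17,508 is a two-group total, that is 8,754 per group.

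**2. The base number.** Standard formula for two proportions, per group:

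n = [1.960 × √(2p̄(1 − p̄)) + 1.282 × √(p₁(1 − p₁) + p₂(1 − p₂))]² / (p₂ − p₁)², with p̄ = (p₁ + p₂)/2.

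| Reading of 3% | p₁ → p₂ | Per group | Two-group total |
|---|---|---|---|
| Absolute, worst case | 48.5% → 51.5% | 5,836 | 11,672 |
| Absolute, at 47.3% | 47.3% → 50.3% | 5,833 | 11,666 |
| Relative, at 47.3% | 47.3% → 48.72% | 26,049 | 52,098 |

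- Absolute: 11,672 is the maximum over all baselines (11,804 with continuity correction). 17,508 / 11,672 = 1.50.
- Relative: the total comes within 3% of 17,508 only for baselines of 71.7% to 72.8%, closest at about 72.2%. At 47.3% the requirement is 52,098 / 17,508 = about 3.0 times the printed number.
- 17,508 / 3 = 5,836, which is exactly the worst-case per-group number for 3 points.

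**3. The secondary outcomes, which set the final size.** Background gives pneumococcal rates of 14.8% to 40.4% and single-digit rates for herpes zoster. Taking these population rates as a guide to the practice rates (an assumption), the two-group totals before clustering are:

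| Baseline | Absolute 3 points | Relative 3% |
|---|---|---|
| 40.4% | 11,366 | 69,212 |
| 14.8% | 6,368 | 272,156 |

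Neither column contains anything near 17,508.

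**4. Power at the printed sizes.** The effective number per group is GPs × cluster size / design effect. Baseline 47.3% assumed.

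| GPs per group, cluster size | Effective n per group | Absolute 3 points | Relative 3% |
|---|---|---|---|
| 868, 48 | 868 × 48 / 4.76 = 8,753 | 97.8% | 46.8% |
| 988, 28 | 988 × 28 / 3.16 = 8,754 | 97.8% | 46.8% |
| 1057, 48 | 1057 × 48 / 4.76 = 10,659 | 99.2% | 54.5% |
| 1057, 28 | 1057 × 28 / 3.16 = 9,366 | 98.4% | 49.4% |

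The 90% is attached to the first two rows. At 1057 GPs and cluster size 48, power under the relative reading is about 30% at a baseline of 30%, 43% at 40%, 59% at 50% and 95% near 72%. Under the absolute reading it stays at 99% or above for all these baselines.

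**5. Detectable absolute difference at 1057 per group, 90% power, baseline near 50%.** Solving the formula in step 2 for p₂ − p₁ gives 2.2 points at cluster size 48 and 2.4 points at cluster size 28.

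**The case against.** Five points can be made for the authors.

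- *The number is attainable.* A relative 3% from a baseline near 72% gives it, and the planning baseline is not printed. This stands, so it would be wrong to say that 17,508 cannot be obtained at all. But Background describes the German rate as low and far from 75%, and a 72% baseline would not carry over to the secondary outcomes, for which the same number is used.
- *The analysis is a pre-post comparison between groups, not a post-only one.* Such a comparison multiplies the two-group total by 2(1 − r), where r is the pre-post correlation. With r = 0.25, 11,672 × 1.5 = 17,508. This shows that another route exists, but Sample mentions no pre-post component and no such correlation.
- *The cause is unknown.* Because 17,508 = 3 × 5,836, a reader might infer that the per-group number was multiplied by three instead of two. The article does not say so, and the pre-post route gives the same figure. The match is suggestive only, and the point does not depend on it.
- *The trial may simply be too large.* True under the absolute reading, where a null result would be more informative than planned and reusing 17,508 for the secondary outcomes is conservative. A reader might infer from the 55% that the trial is underpowered. The article does not support that as a general statement: it requires both the relative reading and a baseline well below 72%.
- *An article condenses a fuller protocol.* An unprinted baseline is therefore not a fault in itself. The fault is that a printed result does not follow from the inputs printed beside it.

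**Conclusion.** The point holds in this form: 17,508 does not follow from the printed inputs for a standard two-group comparison of proportions. Under an absolute 3 points it fails at every baseline and is 50% too large. Under a relative 3% it holds only near a 72% baseline and is about one third of what 47.3% would require. At the sizes to which the stated 90% belongs, power is about 98% or 47%.

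The absolute result needs no assumption about the baseline. The relative result and the power figures assume 47.3%, a 2020/2021 rate, whereas the planning data are described as pre-pandemic. All power figures take the article's intra-cluster correlation and cluster sizes as given. The contrast of 99% with 55% describes 1057 GPs per group, a size that already includes the larger secondary requirement and the 7% reserve, and so should not be set directly against the 90%.

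**What to change.** In Sample, for the influenza outcome and for the secondary outcomes separately:

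1. State the planning baseline and its source. Do not insert 47.3% unless it was the rate actually used.
2. State whether 3% is in percentage points or relative.
3. State the formula, including any pre-post component and the correlation assumed for it.
4. Re-derive the base number and carry it through the patient and GP counts.
5. Keep 1057 GPs per group, but restate what it delivers: either its power under the stated assumptions or its detectable difference. For an absolute effect near 50%, the latter is about 2.2 points at cluster size 48 and 2.4 points at cluster size 28, for 90% power. If a relative 3% was meant, give the power at the planning baseline.

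The cost is a rewritten sample-size paragraph. Recruitment need not change.

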### Measures

#### Secondary data collection

The influenza vaccination rate as primary outcome is measured annually for patients insured by a substitute health insurance fund aged 60 and older. The rate will be computed as the fraction of the amount of vaccinated patients insured by a substitute health insurance fund aged 60 and older and all patients insured by a substitute health insurance fund aged 60 and older of the practice under consideration.

The determination of the secondary outcome, vaccination uptake rates for vaccinations recommended by the STIKO for patients aged 60 and older (except for influenza), is more challenging. This is due to the unclear size of the basic population, which, in turn, is a result of the long periods of time between recommended booster vaccinations (the boosters for tetanus, diphtheria, and pertussis are needed/recommended only every 10 years).

If a sufficiently high number of cases is reached, subgroup analyses for different vaccinations are planned (e.g., for pneumococci and herpes zoster).

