***Summative evaluation (secondary and primary data)***			
**Secondary data**: Extract of pseudonymised contract GP billing data according to § 295 SGB V, n = 2114 GPs (n = 1057 GPs each in the intervention and control group) and at full utilisation ≥ 147,980 patients	**Primary outcome**: Influenza vaccination rate **Secondary outcome**: Vaccination uptake rate of the vaccinations recommended by the STIKO for patients aged 60 and older (except for influenza)	-	Descriptive statistics, pre-post comparison (intervention/control group), cluster analysis, subgroup analyses
**Primary data**: Cross-sectional patient survey in intervention practices (n = 50), pre- and post-implementation (2 x n = 1250 patients), paper & pencil survey	**Secondary outcome**: Vaccine literacy	**Further secondary outcome**: HLS19-VAC-DE subscale of the HLS19 instrument (40)	Descriptive statistics, multivariable regression models, multilevel analysis

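### The primary-outcome design effect uses the number of vaccinated patients (48) as cluster size instead of all eligible patients aged 60 and over. The patient total is about half what the analysis implies, but the planned number of GPs still suffices.

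*Protocol article*

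**What the plan says.** All figures are in the protocol article.

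- **Sample, primary outcome.** The plan assumes that the "influenza vaccination uptake rate as primary outcome increases by 3% as a result of the intervention". It then states that "17,508 patients would be needed without considering the cluster effect" and that "the intra-cluster correlation (ICC) is expected to be 0.08". The inflation is made "With a mean cluster size of 48 patients per practice vaccinated against influenza on average", which gives a design effect of 4.76, 83,338 patients and 1736 GPs (868 per group).
- **Sample, secondary outcome.** "Since the assumed cluster size is reduced to 28, resulting in a design effect of 3.16 with an ICC of 0.08"; this gives 55,325 patients and 1976 GPs (988 per group). The section names this smaller cluster size as the reason why 988 GPs per group are required, and adds 7% to reach 1057.
- **Measures, Secondary data collection.** The influenza rate has vaccinated patients in the numerator and "all patients insured by a substitute health insurance fund aged 60 and older of the practice under consideration" in the denominator. For the other vaccinations, the size of the base population is called unclear.
- **Table 1.** The billing data are expected to cover 2114 GPs and "at full utilisation ≥ 147,980 patients".

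**The concern.** The design effect 1 + (m − 1) × ICC needs m to be the number of patients per cluster on whom the outcome is observed. For a vaccination rate, these are all eligible patients, vaccinated or not. The 48 are described as the vaccinated ones. Every one of them has the outcome, so no proportion can vary among them and no intra-cluster correlation of that proportion applies to them.

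The figure enters twice: in the design effect, and again when 83,338 is divided by 48 to obtain GPs, as if each practice contributed only its vaccinated patients.

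At stake is whether the published justification describes the analysis that will be run, and whether the target of 1057 GPs per group has a stated basis. That target rests on the 28, and the article does not say which patients that number counts.

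**Working it through.** **Inputs.** 17,508 patients before clustering, ICC 0.08, and cluster sizes 48 and 28 (Sample); the denominator definition (Secondary data collection); 47.3% influenza uptake at age 60 and over in 2020/2021 (Background); 2114 GPs and at least 147,980 patients (Table 1). I take 17,508 as stated and, like the article, treat GP and practice as one unit.

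**1. The plan's own figures reproduce.**

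- Primary: 1 + 47 × 0.08 = 4.76; 17,508 × 4.76 = 83,338; 83,338 / 48 = 1736.2, or 868 per group.
- Secondary: 1 + 27 × 0.08 = 3.16; 17,508 × 3.16 = 55,325; 55,325 / 28 = 1975.9, or 988 per group.
- Reserve: 988 × 1.07 = 1057.

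**2. Primary outcome with the eligible-patient denominator.** If 48 patients are vaccinated and uptake is p, the practice has m = 48 / p eligible patients. At p = 0.473:

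- m = 48 / 0.473 = 101.5
- design effect = 1 + 100.5 × 0.08 = 9.04
- patients = 17,508 × 9.04 ≈ 158,200
- GPs = 158,200 / 101.5 ≈ 1559, or 780 per group

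The article gives no baseline rate for the sample size, so p is an assumption. Its range:

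| Assumed uptake | Cluster size m | Design effect | Patients | GPs per group |
|---|---|---|---|---|
| 30% | 160 | 13.72 | 240,210 | 751 |
| 40% | 120 | 10.52 | 184,184 | 767 |
| 47.3% | 101.5 | 9.04 | 158,244 | 780 |
| 50% | 96 | 8.60 | 150,569 | 784 |
| 75% | 64 | 6.04 | 105,748 | 826 |

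**3. Direction of the error.** Combining the steps, GPs per group = (17,508 / 2) × (ICC + (1 − ICC) / m) = 8754 × (0.08 + 0.92 / m). This falls as m grows: 868 at m = 48, 780 at m = 101.5, and never below 8754 × 0.08 = 700. A practice with 48 vaccinated patients has at least 48 eligible ones. At this ICC and this 17,508, the correction can therefore only lower the GP number, whatever the uptake.

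**4. Secondary outcome.** The 28 cannot be all substitute-fund patients aged 60 and over if 48 of them are vaccinated against influenza. It could be a subset, such as patients due for a vaccination. However, the section on secondary data in the summative evaluation says that the data cannot show who had a booster in the past 10 years or who was already vaccinated against pneumococci or herpes zoster. The article does not say what the 28 counts.

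**5. Table 1.** 147,980 / 2114 = 70 patients per GP as a minimum. At m = 70 the design effect is 1 + 69 × 0.08 = 6.52, the patients 17,508 × 6.52 ≈ 114,150, and the GPs 114,150 / 70 / 2 ≈ 815 per group (816 rounded up).

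**The case against.** The strongest reply is that nothing harmful follows. The multiplications are correct, so this is a wrongly defined input and not a slip in arithmetic. For the primary outcome the error is also conservative in the unit that is recruited. Both points stand.

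Four stronger readings are tempting, and the document does not support them:

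- **The trial is underpowered.** A reader might infer this from a patient number that nearly doubles. But eligible patients per practice rise with it, and the GP number falls.
- **The 28 is also a count of vaccinated patients, so the secondary outcome as driver of the size is an artefact.** This is plausible, but the text does not say so. The secondary denominator is left open, so the statement is unsupported rather than refuted.
- **Table 1 contradicts the Sample section with a third cluster size.** Table 1 gives a lower bound. At 101.5 eligible patients per GP the total would be 101.5 × 2114 ≈ 214,600, which satisfies it.
- **One corrected GP number serves both outcomes.** Even with the same cluster size, the number before clustering depends on the baseline rate. The Background gives very different rates: 47.3% for influenza, 14.8% to 40.4% for pneumococci, and single digits for herpes zoster.

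It is also fair to object that 47.3% is a national rate for one season and not a practice-level rate among substitute-fund patients, and that holding the ICC at 0.08 is itself an assumption. The range in the working covers the first. The direction of the result does not depend on the uptake at all, but it does depend on the ICC being held fixed.

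**Conclusion.** For the primary outcome the point holds. The cluster size is the numerator of the rate where the denominator is needed, so 4.76, 83,338, and 1736 (868 per group) are wrong for the analysis as defined. With 17,508 and ICC 0.08 unchanged and an assumed uptake of 47.3%, the design effect is about 9.0 instead of 4.76, and the patients about 158,000 instead of 83,338. Both are higher by a factor of 1.9 (9.04 / 4.76). The GPs are about 780 per group instead of 868, roughly 10% fewer. Over assumed uptake of 30% to 75% the need is 751 to 826 per group. The planned 1057 exceeds every one of these, so no loss of power is shown for the primary outcome.

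For the secondary outcome the finding is narrower: 28 is undefined, and the statement that it sets 988, and hence 1057, GPs per group has no stated support. How many GPs that outcome needs cannot be worked out from the article.

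**What to change.** 1. Take the mean number of eligible substitute-fund patients aged 60 and over per practice from the billing data, and use it as the cluster size for the primary outcome.
2. Define the denominator of the secondary outcome and state its cluster size on the same basis, saying what is counted.
3. Recompute the design effects, patients and GPs for both outcomes, and check the cluster sizes against the minimum of 70 patients per GP that Table 1 implies.
4. Restate the power that 1057 GPs per group gives for each outcome.
5. Revise the sentence naming the secondary outcome as the driver of the sample size if it no longer holds.

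The cost is one recalculation from billing data and a few changed sentences. Recruitment stays as planned.
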